#### Criteria for discontinuing or modifying allocated interventions {11b}

Participants who regained full recovery after initial treatment.Participants who also wish to exit after due counselling.Participants with intractable hypoglycaemia despite maintenance at 12.5% glucose.Participants with dysrhythmias will be unblinded.Participants who develop commodities of severe malaria that could confound the measurable outcomes such as uraemic encephalopathy.Participant with a new disease besides cerebral malaria or updated clinical history related to exclusion criteria.

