### Outcomes {12}

#### The primary outcome

The primary outcome is survival measured at 48 h post-randomization.

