### Sample size {14}

The sample size for this study was calculated using the G*Power calculator, based on the reported outcomes of cerebral malaria with quinine monotherapy (23.0%) and a dual quinine and artesunate combination therapy (12.5%) [10, 18–20]. Going for a difference of 23.0 to 12.5%, a sample size of 470 participants is required accounting for a 10% attrition rate at 80% power of a 2-sided alpha level of significance of 0.05. Based on 1:1 allocation, the treatment arm will have 235 participants and the same number for the control arm. The details of the selected studies for the sample size calculation are shown in a supplementary document as a table.

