#### Plans to promote participant retention and complete follow-up {18b}

The study participants will be contacted via their phone to remind them of the next visit to the neurologist. The transportation fare will be borne by the research sponsor to facilitate retention on follow-up.

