### Methods in analysis to handle protocol non-adherence and any statistical methods to handle missing data {20c}

The result of the study will be analysed per protocol. The number of participants with missing data will be clearly stated, and the missing items will be mentioned.

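### A child whose family leaves before 48 h can drop out of the primary mortality comparison, because the plan counts missing outcomes but describes no way of obtaining them

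*Protocol article*

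**What the plan says.** All references are to the protocol article.

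- **The primary outcome:** "The primary outcome is survival measured at 48 h post-randomization".
- **Sample size {14}:** "a sample size of 470 participants is required accounting for a 10% attrition rate". The section does not say when this attrition occurs or whether it means unknown vital status.
- **Discontinuing or modifying interventions {11b}:** the list includes "Participants who also wish to exit after due counselling". Neither this section nor any other says whether such a child's 48 h status is still collected.
- **Retention {18b}:** "The study participants will be contacted via their phone to remind them of the next visit to the neurologist". Transport is also paid. No other follow-up contact is described.
- **Non-adherence and missing data {20c}:** the analysis is per protocol, and for missing data the text adds only "The number of participants with missing data will be clearly stated, and the missing items will be mentioned".
- **Statistical methods {20a}:** chi-squared or Fisher's exact tests for categorical outcomes, with Kaplan-Meier and Cox methods also named for survival. How children who leave are treated is not stated.

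**The concern.** Section {20c} is not silent. It fixes an analysis set and limits the handling of missing outcomes to a tally. Taken with {11b} and {18b}, a child removed from hospital before 48 h has no described route back into the primary comparison, either through data collection or through the analysis.

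A family may leave because the child is doing badly or because the child has recovered, so leaving is plausibly related to the outcome itself. Under {11c}, families also bear costs outside the trial. If deaths among leavers differ between arms, a risk difference computed without them is biased, and the direction cannot be known in advance. Inflating the sample size restores power but does nothing about this bias. An analysis plan written later cannot repair it either, because an outcome never collected cannot be analysed.

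**Working it through.** **Inputs.** From {14}: rates of 23.0% and 12.5% (read here as mortality), two-sided alpha 0.05, 80% power, 1:1 allocation, 470 in total (235 per arm), 10% attrition. From {20a}: chi-squared or Fisher's exact test. Assumptions, not in the article: the share lost before 48 h and the mortality of leavers. Both are varied below.

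**1. Reproducing the plan's figure.** With pooled variance under the null,

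n per arm = [1.960·√(2·p̄·q̄) + 0.842·√(p₁q₁ + p₂q₂)]² / (p₁ − p₂)², where p̄ = 0.1775.

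This is (1.0591 + 0.4505)² / 0.105² = 206.7, so 207 per arm and 414 in total. Dividing by 0.9 gives 460, within 3% of the stated 470. Power with 211 analysed per arm is 80.8%, so a 10% loss is covered as far as power goes.

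**2. If the whole 10% were lost before 48 h.** 0.10 × 470 = 47 children, taken as 24 control and 23 dual. Observed deaths at the design rates are 0.23 × 211 ≈ 49 and 0.125 × 212 ≈ 26, 75 in all. The test is z = (p₁ − p₂)/√[p̄(1 − p̄)(1/n₁ + 1/n₂)], which is chi-squared without continuity correction. For 49/211 v 26/212, z = 0.1096/0.0371 = 2.95, p=0.003.

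The 47 are then put back with assumed outcomes, with 235 per arm:

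| Missing control (24) | Missing dual (23) | Deaths, control v dual | p, chi-squared |
|---|---|---|---|
| all alive | all alive | 49 v 26 | 0.004 |
| all dead | all dead | 73 v 49 | 0.012 |
| 6 die (23%) | 12 die (about 50%) | 55 v 38 | 0.049 |
| 6 die (23%) | 13 die | 55 v 39 | 0.065 |
| 6 die (23%) | 14 die (about 60%) | 55 v 40 | 0.085 |
| all alive | 7 die | 49 v 33 | 0.052 |
| all alive | all dead | 49 v 49 | 1.0 |

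With control leavers dying at 23%, chi-squared significance is lost at 13 of 23 deaths among dual-arm leavers. By Fisher's exact test it is lost at 12 of 23 (p=0.064). Similar mortality in both groups of leavers leaves the result significant.

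**3. If the loss before 48 h is smaller.**

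- **2% (5 per arm):** observed 53/230 v 29/230. In the worst case, with missing dual children dead and missing control children alive, deaths are 53 v 34 of 235, p=0.024. The result stands.
- **5% (12 per arm):** observed 51/223 v 28/223. The worst case is 51 v 40 of 235, p=0.20. With leavers dying at 23% in control and 60% in dual, the result is (51 + 3) v (28 + 7) = 54 v 35 of 235, p=0.025, still significant.

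The conclusion therefore depends on two unknowns together: how many leave before 48 h, and how differently leavers fare by arm.

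**The case against.** The strongest reply is that early loss should be small. The participants are inpatients with impaired consciousness, treatment is scheduled to 72 h, the participant timeline records survival at 12, 24, 48 and 72 h, and fatal events are reportable within 24 h. A child seen on day 29 was plainly alive at 48 h. This stands, and it is why the 10% figure cannot be taken as the expected loss. It does not close the gap. Those provisions work while the child is in hospital or comes back. A day-29 visit can confirm survival, but it cannot reveal a death at home.

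A reader might infer from {14} that the plan accepts 47 children without a 48 h outcome. The article does not support that: the allowance could equally cover loss by day 29 or removal from the per-protocol set. A reader might also infer that exits will differ by arm. Nothing in the article shows this. Caregivers and clinicians are blinded, and {11c} has the trial pay for managing adverse events from the intervention. Differential exit is a risk, not a documented fact, and the 60% mortality used above has no source in the article.

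Two further points have partial force. Kaplan-Meier and Cox methods would use leavers' time until exit, but censoring them is valid only if leaving is unrelated to prognosis, which is the assumption in doubt. Detailed sensitivity analyses are commonly left to an analysis plan, so their absence alone is no fault. The fault lies in what {20c} does state and in the lack of a described route to vital status.

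**Conclusion.** The point holds as a weakness in data collection and analysis set. As written, a child who leaves before 48 h can fall out of the primary comparison for reasons tied to outcome. It does not hold as a claim that a tenth of the outcomes will be missing or that the result will be decided by them. On the plan's own rates, overturning the full planned effect takes both a loss well above 2% and markedly different mortality among leavers by arm. At 10% loss, with control leavers dying at 23%, more than half of the dual-arm leavers would have to die. A true effect smaller than planned would have less margin. The change is worth making but is not critical, and since the article gives the trial status as not recruiting, it can still be made cheaply.

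**What to change.** 1. **{11b} and {18b}:** state that stopping trial treatment does not end follow-up, and that 48 h vital status will be obtained by phone for every randomised child who leaves, unless the family refuses. This is a rule about data collection and changes no treatment criterion.
2. **{20c}:** include these children in the primary analysis by randomised arm, in place of the per-protocol rule. Without this the phone call achieves nothing, because a leaver with known status could still be excluded.
3. **{20c}:** for any child still unknown, pre-specify a best/worst-case or tipping-point analysis that varies mortality separately by arm. This is secondary to the first two steps.

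The cost is one call for each departing family and one extra table, with no added participants.

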### Plans to give access to the full protocol, participant-level data, and statistical code {31c}

The protocol shall be published in a peer-reviewed journal and made publicly accessible to interested individuals or bodies. The participant-level dataset and statistical code shall be made available after following due process adhering to good ethical standards.

### Oversight and monitoring

#### Composition of the coordinating centre and trial steering committee {5d}

A trial steering committee will consist of the principal investigator, two scientific enquiries, the public enquirer, and a biostatistician. They will meet frequently to provide an oversight function for the trial conduct over the four centres in the country.

Each centre will have a hospital trial group headed by a consultant paediatrician who will be saddled with running daily events in the hospital, providing organizational support and reporting on a weekly basis to the steering committee. All investigators and monitors will be GCP compliant.

#### Composition of the data monitoring committee, its role, and reporting structure {21a}

The Data Safety and Monitoring Board DSMB will consist of a multi-disciplinary team of five professionals from the University College Hospital Ibadan. They will have oversight monitoring and safety checks on the data quality and interim analysis of the trial data. They will ensure conformity to the trial protocol. In the event of the inferiority of the primary and secondary outcomes of the trial compared with the standard of care and in the event of worse adverse reactions in the experimental arm, the trial would rely upon the extensive data safety review of the DSMB and the clinical pharmacologist to evoke a stopping rule on the trial.

#### Adverse event reporting and harms {22}

All participants in this trial will be monitored for medication side effects and adverse events. An adverse event (AE) is any untoward medical occurrence which happens to a participant on a trial. All AEs will be reported in the case report form (CRF) regardless of suspected causality. Medidata rave will be used for reporting of AEs. Serious adverse events (SAEs) include fatal medical occurrences, life-threatening, that require or prolong hospitalization or cause congenital anomaly or permanent or significant disability or incapacity. All SAEs will be reported to the sponsor, Local Health Research Ethics and DSMB, and Trial Steering Committee within 24 h.

#### Frequency and plans for auditing trial conduct {23}

The local ethics board will monitor the progress of this trial, and all medications and updates will be relayed to the body as events unfold. There will be weekly monitoring of trial sites.

#### Plans for communicating important protocol amendments to relevant parties {25}

Any modification to the protocol or trial update will be communicated to the ethical approval bodies, trial registry, and any other relevant parties within 24 h.

#### Dissemination plans {31a}

The outcome of this study will be communicated to participants, ethics board, and healthcare professionals. It will be published in peer-reviewed scientific journals for public access. Data will be made available to the public maintaining ethical guidance.

## Discussion

The outcome of this analysis will give insight into the efficacy and safety of dual intravenous artesunate plus quinine compared to artesunate only in the treatment of cerebral malaria in Nigerian children. The safety profile of this intervention will also be highlighted. This may help inform physicians on a better option for the treatment of cerebral malaria to improve outcomes; prevent the development of resistance, recrudescence, and treatment failure; and stimulate the interest of pharmaceutical companies in the development of newer formulations of dual intravenous antimalarial combination therapies.

## Trial status

The trial is active but not recruiting.

## Abbreviations

RCT: Randomized controlled trial
PACTR: Pan Africa Clinical Trial Registry
GCMS: Glasgow Coma Score
GCP: Good Clinical Practice
MGCS: Modified Glasgow Coma Score
LMIC: Low- and middle-income countries
HIV: Human immunodeficiency syndrome
AIDS: Acquired immunodeficiency syndrome
